#### 1.12.2.2 Definition of serious adverse events

A serious adverse event (SAE) is any untoward medical occurrence that at any dose:

1. Results in death,
2. Is life-threatening\*,
3. Requires inpatient hospitalization or prolongation of existing hospitalization,
4. Results in persistent or significant disability / incapacity,
5. Is a suicide attempt.

\*NOTE: The term ‘life-threatening’ in the definition of ‘serious’ refers to an event in which the subject was at risk of death at the time of the event; it does not refer to an event, which hypothetically might have caused death if it was more severe.

An elective hospital admission will not be considered a serious adverse event.

#### 1.12.2.3 Definition of intensity of adverse events

The following categories will be used for the rating of the intensity of adverse events:

**Table 3:** Intensity of adverse events

|          |                                                                                                            |
|----------|------------------------------------------------------------------------------------------------------------|
| Unclear  | inadequate data, that are not sufficient for assessment                                                    |
| Mild     | Causing no limitation of usual activities; the subject may experience slight discomfort                    |
| Moderate | Causing some limitation of usual activities; the subject may experience annoying discomfort                |
| Severe   | Causing inability to carry out usual activities; the subject may experience intolerable discomfort or pain |

#### 1.12.2.4 Definition of serious adverse event and adverse event causality

A determination of the relationship between an SAE or AE and the treatment must be made after due consideration by the Investigator for each SAE or AE at every visit.

The assessment of the relationship of an SAE or AE to the administration of treatment is a clinical decision based on all available information at the time of and after the occurrence of the event.

The factors which may be considered when evaluating the relationship of an SAE or AE to the treatment include: time from exposure to treatment until onset of the event; recovery or improvement on discontinuation of treatment; availability of alternative explanations such as underlying or intercurrent diseases; concomitant medications or treatments; known response pattern for this treatment; recurrence on reintroduction of treatment.

The relationship of serious adverse events and adverse events to the treatment will be assessed according to the following categories:

- “definite”: A clinical event with a reasonable temporal relationship to the administration of the treatment. AE cannot be explained by concomitant diseases or other drugs or chemicals. AE must be phenomenologically unambiguous.
- “probable”: A clinical event in a reasonable time sequence to administration of the treatment. AE is unlikely to be attributed to concurrent disease or other drugs or chemicals.
- “possible”: A clinical event in a reasonable time sequence to administration of the treatment, but AE could also be explained by concurrent diseases or other drugs or chemicals.

- “unlikely”: A clinical event with a weak temporal relationship to administration of the treatment. Other factors, such as the underlying, concomitant diseases, concomitant medication, are plausible to have contributed to the event.
- “not related”: No relationship to administration of treatment, i.e., there is a clear alternative explanation, an unreasonable temporal relationship between the drug and the event, or relationship is otherwise not plausible.
- “not determinable”: inadequate data, that are not sufficient for assessment.

#### 1.12.2.5 Definition of measures in case of serious adverse event and adverse event

The measures taken in case of AEs will be described according to the following 4 categories:

1. None / treatment continued,
2. Treatment interrupted,
3. Treatment discontinued,
4. Other

The measures taken in case of SAEs will be described according to the following 8 categories:

1. None / treatment continued,
2. Inpatient hospitalization,
3. Non-pharmacological measures,
4. Pharmacological measures,
5. Treatment interrupted,
6. Treatment discontinued,
7. Other.

#### 1.12.2.6 Definition of serious adverse event and adverse event outcome

The outcome of AEs will be described according to the following 5 categories:

1. Resolved,
2. Resolving/solution in process,
3. Not Resolved,
4. Resolved with sequelae,
5. Unknown.

The outcome of SAEs will be described according to the following 6 categories:

1. Resolved,
2. Resolving/solution in process,
3. Not Resolved,
4. Resolved with sequelae,
5. Fatal,
6. Unknown.

#### 1.12.2.7 Suicidality

Suicidality will be assessed at the screening/baseline visit and every following visit during assessment of serious adverse events and adverse events (see section 13.2.1.). Suicidality assessment will include the occurrence of passive suicidal thoughts, active suicidal intentions or plans and suicide attempt since the last visit. The Investigator has to determine the intensity, risk level, causality (study-related or not), measures and outcome.

A determination of the relationship between suicidality and the treatment must be made after due consideration by the Investigator. The assessment of the relationship of suicidality to the administration of treatment is a clinical decision based on all available information at the time of and after the occurrence of the event.

The factors which may be considered when evaluating the relationship of suicidality to the treatment include: time from exposure to treatment until onset of suicidality; recovery or improvement on discontinuation of treatment; availability of alternative explanations such as underlying or intercurrent diseases; concomitant medications or treatments; known response pattern for this treatment; recurrence on reintroduction of treatment.

In case of suicidality (see section 13.2.1. and 13.2.2.) the Investigator has to determine the risk level:

**Table 4:** Suicidality risk level

|                 |                                                                                                                                                                                                                                                                                                                                                      |
|-----------------|------------------------------------------------------------------------------------------------------------------------------------------------------------------------------------------------------------------------------------------------------------------------------------------------------------------------------------------------------|
| Low risk:       | The patient has passive suicidal ideations but no suicidal intentions, plans or active wish to commit suicide. The Investigator/study personnel should pay attention to suicidality and assess the change of status carefully at every visit. The patient must be informed about help services and emergency plans in case of worsening of symptoms. |
| Increased risk: | The patient has suicidal intentions or plans but no active wish to commit suicide. This is an urgent situation. The Investigator/study personnel have to ensure that the patient is being seen by a psychiatrist within 24 hours. The patient must be informed about help services and emergency plans in case of further worsening of symptoms.     |
| Acute risk:     | The patient has active suicidal intentions or plans. Self-control or external social support might be lacking (e.g. family, friends) or unclear. The study personnel must immediately initiate the admission of the patient to a psychiatric inpatient unit.                                                                                         |

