### 1.10.2.4 Exclusion criteria

Any of the following will exclude a subject from the trial:

| Exclusion criteria                                                                                      |
|----------------------------------------------------------------------------------------------------------------|
| • Bipolar depression                                                                                           |
| • Schizophrenia                                                                                                |
| • Other psychotic disorders                                                                                    |
| • Substance abuse or dependency                                                                                |
| • Dementia                                                                                                     |
| • Acute suicidality                                                                                            |
| • Anxiety disorder as stand-alone diagnosis (e.g. generalized anxiety disorder, panic disorder, social phobia) |

| Exclusion criteria                                                                                                                  |
|--------------------------------------------------------------------------------------------------------------------------------------------|
| • Obsessive-compulsive disorder as stand-alone diagnosis                                                                                   |
| • Participation in any another clinical trial parallel to this trial                                                                       |
| • Additional psychological/psychotherapeutic treatment throughout the treatment period                                                     |
| • Regular use with scheduled dosing of Benzodiazepines (not PRN)                                                                           |
| • Severe or instable medical condition, which clearly impacts on depression or on the ability to participate in the trial                  |
| • Brain disease with severe functional impairment that impacts the ability to participate in the trial (e.g. aphasia, Parkinson's disease) |

Any of the following will exclude a subject from the Magnetic Resonance Imaging (MRI) acquisition, if applicable:

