##### 1.10.4.3 Premature termination of the trial

The trial will be stopped for the individual study participant, if the individual:

- Withdraws the informed consent.
- Develops a medical condition, which prevents participation in the trial.
- Experiences worsening of depression, which requires inpatient treatment or change of antidepressive medication.
- Develops acute suicidality.

The trial may be prematurely terminated by the respective competent local EC or the Lead Principal Investigator, if:

- The perception of the benefit/risk ratio becomes unfavourable for the continuation of the trial.
- The risk-benefit balance for the trial subject changes markedly.
- It is no longer ethical to continue treatment.
- It is no longer practicable to complete the trial.

However, our trial and study protocol are not to be expected to harm any subject but to improve outcomes. We do not expect that the trial has to be stopped in advance.

A decision to cease the trial is binding on all Investigators. Clinical Trials Centre Cologne, as well as the principal Investigators in each centre, must be informed immediately on the discontinuation of the trial. If the trial is prematurely terminated or suspended for any reason, the Investigator should promptly inform the subjects, should assure appropriate follow-up for the subjects, and inform the institution where the trial was being performed.

Participating centres, which fail to include the estimated number of subjects or to guarantee treatment in accordance to study protocol, will be closed.

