| ISI/ESS/RBDSQ                                              |                | ●        |           |    |    |    |    |    |    | ●  |    |    |    |    |    |    |    |    | ●                | ●         |
| CERADplus                                                  |                | ●        |           |    |    |    |    |    |    |    |    |    |    |    |    |    |    |    |                  | ●         |
| NAB subtest maze                                           |                | ●        |           |    |    |    |    |    |    |    |    |    |    |    |    |    |    |    |                  | ●         |
| LIFE                                                       |                |          |           |    |    |    |    |    |    |    |    |    |    |    |    |    |    |    |                  | ●         |
| Treatment (CBT or SUI)                                     |                |          | ●         | ●  | ●  | ●  | ●  | ●  | ●  |    | ●  | ●  | ●  | ●  | ●  | ●  | ●  | ●  |                  |           |
| Evaluation of SAEs, AEs b) , exclusion criteria |                |          | ●         | ●  | ●  | ●  | ●  | ●  | ●  | ●  | ●  | ●  | ●  | ●  | ●  | ●  | ●  | ●  | ●                | ●         |
| Assessment of medical history                              |                |          |           |    |    |    |    |    |    |    |    |    |    |    |    |    |    |    |                  | ●         |
| Voluntary procedures:                                      |                |          |           |    |    |    |    |    |    |    |    |    |    |    |    |    |    |    |                  |           |
| Blood sampling c)                               |                | ●        |           |    |    |    |    |    |    | ●  |    |    |    |    |    |    |    |    | ●                | ●         |

|                   | TRIAL SCHEDULE |          |           |   |   |   |   |   |   |   |    |    |    |    |    |    |    |    |                  |           |    |    |
|-------------------|----------------|----------|-----------|---|---|---|---|---|---|---|----|----|----|----|----|----|----|----|------------------|-----------|----|----|
| Procedure         |                |          |           |   |   |   |   |   |   |   |    |    |    |    |    |    |    |    |                  |           |    |    |

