#### 1.12.2 Adverse events

##### 1.12.2.1 Definition of adverse events

An adverse event (AE) is any untoward medical occurrence in a patient or clinical investigation subject which does not necessarily have a causal relationship with this treatment. An AE can therefore be any unfavorable and unintended sign, symptom, or disease temporally associated with the treatment, whether or not considered related to the treatment.

In this study adverse events are defined and assessed as:

1. Worsening of symptoms e.g. generalisation of symptoms,
2. Occurrence of new symptoms,
3. Occurrence of passive suicidal thoughts,
4. Occurrence of active suicidal intentions or plans,
5. Occurrence of problems in the patient-therapist relationship,
6. Private problems,
7. Occupational problems,
8. Further adverse events (e.g. Influenza, fractures etc.).

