##### 2.4.3.1 Safety/Tolerability

- Adverse events
- Serious adverse events
- Assessment of suicidality

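### The planned adverse-event table does not separate suicidal ideation persisting from entry from new onset, because the SAP never uses the baseline suicidality level (minor, cheap to fix)

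*Combined protocol and SAP*

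**What the plan says.** **Timing.** Section 1.12.2.7 places the suicidality assessment at screening/baseline and at each later visit, inside the AE/SAE assessment: "Suicidality will be assessed at the screening/baseline visit and every following visit during assessment of serious adverse events and adverse events". In Table 2 (section 1.11.2) the row for that assessment, "Evaluation of SAEs, AEs b) , exclusion criteria", is ticked at visits 2 to 19 and blank at SCR and T0. No row names suicidality.

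**Content.** Section 1.12.2.7 continues: "Suicidality assessment will include the occurrence of passive suicidal thoughts, active suicidal intentions or plans and suicide attempt since the last visit". Where suicidality is present, the investigator assigns a Table 4 level: low, increased or acute. At the low level, staff are told to "assess the change of status carefully at every visit".

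**Entry.** The only suicidality exclusion in section 1.10.2.4 is "Acute suicidality".

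**Event definitions.** Section 1.12.2.1 makes "Occurrence of passive suicidal thoughts" AE category 3 and active intentions or plans category 4. Neither requires the event to be new or worse than at entry. Worsening of symptoms and new symptoms are categories 1 and 2. A suicide attempt is an SAE (1.12.2.2).

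**Stopping.** The trial stops for a participant who meets "Develops acute suicidality" (1.10.4.3).

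**Analysis.** SAP 2.4.3.1 lists "Assessment of suicidality" as a safety variable beside AEs and SAEs. SAP 2.6.4.1 provides listings of AEs and SAEs by subject and arm. SAP 2.6.4.1.1 adds a summary by group, category, seriousness, severity and relatedness. Neither refers to the baseline level.

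**The concern.** Section 1.7.1 names transient worsening of symptoms and risk of suicidality as possible undesired effects of psychotherapy. The natural safety question is therefore whether suicidality emerged or worsened after treatment began, arm by arm. In moderate to severe late-life depression, some patients may already have passive thoughts when they enter, and the entry criteria allow this.

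If such a patient still has passive thoughts at visit 2, the category 3 wording permits an AE entry. That entry then sits in the same row of the by-arm table as a patient whose thoughts began during treatment. The level needed to separate the two is one the protocol already asks staff to assess, but the schedule does not prompt for it at the visits that define baseline and the SAP does not use it. At stake is how clearly a descriptive safety table reads, not the primary result and not participant protection.

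**Working it through.** The documents contain no suicidality rate, so there is no stated figure to reproduce on this point. The check is a reading of the text, followed by an illustration with assumed inputs.

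**Step 1: can persisting ideation enter the table?**
- Entry (1.10.2.4): only acute suicidality excludes. Read with Table 4, patients at the low level (passive ideation) and the increased level (intentions or plans without an active wish) are not excluded on this ground.
- Recording (1.12.2.1): categories 3 and 4 are defined by occurrence, with no condition relative to entry.
- Summary (SAP 2.6.4.1.1): counts are by category, with no rule restricting them to events that emerge on treatment.

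So it can. The overlap is mainly in category 3 (passive thoughts), with some possible in category 4 for a patient who entered at the increased level.

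**Step 2: what is already kept apart?** A patient who moves from passive thoughts to plans moves from category 3 to category 4, and an attempt becomes an SAE. Persisting passive ideation is therefore not mixed with those escalations.

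**Step 3: is the baseline level available and used?** Section 1.12.2.7 requires it. In the Table 2 AE row, 0 of the 2 pre-treatment columns and all 18 columns from visit 2 to visit 19 are ticked. Footnote b starts AE recording at consent, but only for events that are volunteered or noticed, which is not an active baseline assessment. SAP 2.4.3.1, 2.6.4.1 and 2.6.4.1.1 contain no baseline comparison.

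**Step 4: illustration, every rate assumed.** The group size is the planned 124 per arm (SAP 2.1.7: 99/0.8 = 123.75, rounded up); the safety set could be slightly smaller. Let *b* be the share with ideation at entry, half of it persisting, and let new onset be 5% v 10% of the rest.
- New onset only: p1 = (1 − b) × 0.05 and p2 = (1 − b) × 0.10.
- All persisting ideation counted: add 0.5 × b to each arm.
- 95% half-width = 1.96 × √[(p1(1 − p1) + p2(1 − p2))/124].

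For b = 20%: 0.80 × 0.05 = 4% and 0.80 × 0.10 = 8%; half-width = 1.96 × √[(0.0384 + 0.0736)/124] = 5.9 points. Adding 0.5 × 0.20 = 10% gives 14% v 18%; half-width = 1.96 × √[(0.1204 + 0.1476)/124] = 9.1 points.

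| Ideation at entry | New onset only | Half-width | Persisting also counted | Half-width | Widening | Ratio | Difference |
|---|---|---|---|---|---|---|---|
| 10% | 4.5% v 9% | 6.2 | 9.5% v 14% | 8.0 | 1.29 | 2.0 → 1.47 | 4.5 both ways |
| 20% | 4% v 8% | 5.9 | 14% v 18% | 9.1 | 1.55 | 2.0 → 1.29 | 4.0 both ways |
| 30% | 3.5% v 7% | 5.5 | 18.5% v 22% | 10.0 | 1.81 | 2.0 → 1.19 | 3.5 both ways |

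If only half of the persisting ideation is recorded at b = 20%, the table reads 9% v 13%, with half-width 7.8 points and ratio 1.44. In every row the expected absolute difference is unchanged, because randomization adds the same expected count to both arms. The ratio and the precision are what suffer.

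**The case against.** The strongest reply is that the plan already handles suicidality. Section 1.12.2.7 requires the baseline assessment in words. Acute suicidality cannot be ruled out at screening without asking about suicidality. Categories 3 and 4 and the SAE definition carry suicidality into the analysis, by-subject listings allow a manual comparison, and AE outcomes such as not resolved (1.12.2.6) let one event be carried forward instead of re-entered. Safety data go to the DSMB continuously (1.12.2.8). Nothing says staff will log ideation present at entry as a fresh event, and the rates above are invented.

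Most of this stands, and it rules out several stronger inferences that a reader might draw:
- *That baseline suicidality goes unassessed.* The blank cells conflict with section 1.12.2.7; they do not show that the data are not collected.
- *That suicidality drops out of the analysis,* because SAP 2.6.4.1 names only AEs and SAEs. It is included through those categories.
- *That no entry for absence of suicidality can be recorded.* That depends on the eCRF (1.13.2), which is developed separately and is not in the documents.
- *That the comparison is biased or participants are less safe.* No direction is shown, and the Table 4 actions and the stopping rule apply whatever the table looks like.

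What the reply does not supply is a planned by-arm summary against the entry level. The change-of-status instruction and the relatedness judgement guide individual care and causality. A manual comparison from listings is unplanned and needs a recorded baseline level.

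**Conclusion.** The concern holds as a minor point and a cheap improvement. Suicidality is analysed only through AE/SAE categories that ignore the entry level, and non-acute ideation is allowed at entry. The by-category table can therefore mix persisting with new ideation, mainly passive, with some in category 4 for patients entering at the increased level. The schedule leaves the required baseline assessment unmarked, and the SAP does not use it.

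The conclusion rests on the text and on one condition: that staff record persisting ideation as an occurrence, which the wording permits but does not require. Its size is unknown. The illustration (ratio falling from 2.0 to between 1.47 and 1.19, half-width 1.29 to 1.81 times as wide, absolute difference unchanged) rests wholly on assumed rates and is not a trial figure. The safety analysis is descriptive, so no test is affected.

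**What to change.** 1. In Table 2, mark the suicidality assessment at SCR/T0. Record there the Table 4 level, or none, and state the recall window that applies at that first assessment, since the window given in section 1.12.2.7 looks back to a previous visit.
2. In SAP 2.6.4.1, add one descriptive by-arm shift table in the safety set: baseline level (none, low, increased) by worst post-baseline level (none, low, increased, acute, attempt). Take the worst level over all post-baseline visits, because a participant who develops acute suicidality is stopped and may have no later assessment. Read it as counts, without a test.

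The AE listings, the category summary and the Table 4 actions stay as they are. The cost is a few extra baseline entries and one extra table whose increased, acute and attempt cells will be sparse. No new visit is needed, because section 1.12.2.7 already requires the assessment.
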